### Blinding

Both the person evaluating the VHI and the participants will not be informed about the group assignments. This ensures that neither the evaluator nor the participants know which group the participants are in (blinding).

### Outcomes

#### Questionnaires

A questionnaire will be administered to the participants during their initial outpatient consultation conducted by the researcher to gather sociodemographic information.

To assess quality of life and sexual satisfaction, validated questionnaires in Brazil will be employed. The Female Sexual Function Index (FSFI) is a tool used to evaluate female sexual response across six domains: desire, arousal, lubrication, orgasm, satisfaction, and pain [30, 31].

The International Consultation on Incontinence Questionnaire—Short Form (ICIQ-SF) is a questionnaire designed to assess the impact of Urinary Incontinence (UI) on quality of life and quantify urinary loss in both male and female patients [32].

The methods for evaluating Genitourinary Syndrome of Menopause (GSM), which describe the participants’ perception of clinical symptoms before and after the proposed treatment, include the Vaginal Health Index Score (VHI). This method encompasses a clinical assessment during a speculum examination, covering five parameters: elasticity, pH, mucosal appearance, moisture, and the presence of vaginal secretion. A qualified healthcare professional will conduct this evaluation during the physical examination, allowing for the diagnosis of Vulvovaginal Atrophy (VVA) [33].

Vaginal pH evaluation will be performed using a pH indicator strip inserted into the middle third of the vagina, in contact with the mucosa, causing a color change in the strip. The nitrazine strip should remain in contact with the vaginal wall for 5 seconds before checking the pH on the colorimetric scale provided by the manufacturer [34].

The Visual Analog Scale (VAS) will be applied as an instrument for assessing the intensity of pain reported by the participants, aiming to monitor the progression of GSM symptoms during treatment. This assessment will be conducted for each of the symptoms, such as dyspareunia, dryness, irritation/burning, itching, and cytorrhagia, both before and after treatment [35].

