### Contextualization

Genitourinary Syndrome of Menopause (GSM) refers to a set of symptoms and signs associated with estrogen deficiency, characterized by changes in the genitourinary organs resulting in various urinary, genital, and sexual alterations [1].

GSM or its characteristics manifest in approximately 15% of women in the premenopausal stage and 40–54% of women in the postmenopausal stage [2, 3]. In the United States, GSM is estimated to affect 8% to 22% of women in the premenopausal stage and 40% to 57% of women in the postmenopausal stage. Surprisingly, only 1 in 5 women experiencing GSM-related symptoms seek medical attention [4]. International literature indicates that only 59% of these women seek medical help, whereas in Europe, only 4% of women report vulvovaginal symptoms. About 25% of women with GSM seek medical care, and only 54% discuss their sexual health with healthcare professionals when asked, while 33% choose not to address this issue during a consultation [5].

In Brazil, studies show that only 59% of women experiencing symptoms related to urogenital atrophy seek medical help. The complaint of vaginal dryness is present in 34.9% of women, and respondents reported that the climacteric negatively impacts their sexuality. In the United States, 59% of women reported sexual dissatisfaction [6–8].

Among the observed signs and symptoms, studies found a high frequency of complaints such as dyspareunia (44%), irritation (37%), vaginal dryness (55%), recurrent urinary tract infections (5% to 17%), and urge incontinence in women above 60 years (15% to 35%). The prevalence of atrophic vaginitis was 4%, increasing to 25% in the first year after menopause and 47% after three years. Note that dyspareunia leads to a reduction in the frequency of sexual intercourse, with 72% of women having intercourse only once a month and 34% weekly [9, 10].

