### Sample size and participants

Since the literature lacks studies on the effects of the photobiomodulaton on GSM, the sample size was calculated using the formula described using the estimated effect size, as described by Kadam and Bhalerao [29]. Considering a type I error of 0.05 and a test power of 80%, the calculated sample size was 60 participants, with 30 in each group (A and B). The Fig 3 shows that, for medium (0.750) and large effects (1.000–1.250), a minimum of 30 patients per group is sufficient to control statistical variance, ensuring a test power greater than 0.80. Considering a 10% of sample loss, a total of 66 patients will be recruited for the study. The Fig 3 shows a plot of the test power as a function of the sample size and estimated effect size.

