### Inclusion and exclusion criteria

#### Inclusion

Women over 50 years old in the postmenopausal period (amenorrhea for at least 12 months without involved pathology);Presenting one or more symptoms of GSM (such as dyspareunia, dryness, irritation, vaginal burning and/or discomfort, vaginal and vulvar atrophy, vaginal dryness, dysuria, polyuria, recurrent urinary infections);With complaints of stress and/or urgency urinary incontinence;Presenting a normal cervical cytology (Pap smear) performed within the last year.

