### Statistical analysis

The data will be tested for normality using the Shapiro-Wilk test, and those with parametric distribution will be represented by their respective means and standard deviations. In cases where the assumption of parametric distribution is rejected, medians and quartiles will be used. To assess the association between the studied groups and the independent variables, Student’s t-test or Wilcoxon-Mann-Whitney test will be used for parametric and non-parametric data, respectively. All tests will be two-tailed, and the adopted significance level is α = 0.05. The results will be organized in excel spreadsheet and the inferential analysis will be conducted using R.

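### Symptom VAS scales: entry needs only one GSM symptom, so separate unadjusted comparisons on each scale may fall well below the stated 80% power

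*Protocol article*

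**What the plan says.** Inclusion criteria: a woman qualifies on "Presenting one or more symptoms of GSM". The examples listed include dysuria, polyuria and recurrent urinary infections as well as dryness, dyspareunia and irritation. Every woman must also enter "With complaints of stress and/or urgency urinary incontinence". No minimum symptom score is set.

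Outcomes, Questionnaires: the VAS is taken symptom by symptom, at baseline and again after treatment: "This assessment will be conducted for each of the symptoms, such as dyspareunia, dryness, irritation/burning, itching, and cytorrhagia". None of the five named symptoms is a urinary one.

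Statistical analysis: groups are compared by Student's t-test or the Wilcoxon-Mann-Whitney test, with the choice governed by a Shapiro-Wilk test. "All tests will be two-tailed, and the adopted significance level is α = 0.05". The section mentions neither baseline adjustment nor a subset with the symptom, and it does not say whether final values or changes are compared.

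Sample size and participants: 30 women per group are said to give more than 80% power for standardised effects from 0.75 upwards. The effect is not tied to any outcome.

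Contextualization gives background frequencies of 55% for dryness, 44% for dyspareunia and 37% for irritation. It gives none for itching or cytorrhagia.

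**The concern.** Who enters, what is measured and how it is tested do not fit together. A woman who enters with dryness alone scores at or near zero on dyspareunia, irritation/burning, itching and cytorrhagia. A woman who enters with dysuria alone may score zero on all five named scales. On a scale where she starts at zero she has no room to improve, whatever the treatment does.

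If all women are compared on every scale, which is the natural reading, such women affect the comparison in two ways. They shrink the mean difference between groups. On final values they also add a large spread between women with and without the symptom. The sample size statement assumes that all 30 women per group can show the effect, so its power does not transfer to these comparisons.

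The Discussion states a hypothesis of symptom relief, and the VAS is the most direct patient-reported measure of it. A real benefit could be missed on several scales. With several tests each at 0.05, an isolated significant scale would be hard to interpret.

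**Working it through.** **1. The plan's own figure.** With a standardised effect of 0.75, 30 per group and two-sided α = 0.05, power is 0.815 (exact t) or 0.828 (normal approximation). The stated power is reproduced, provided every woman can respond.

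**2. Share at zero (assumption).** The protocol does not give symptom shares for its entrants. Two bounds follow from its background frequencies.
- Carried over unchanged: 1 − 0.55 = 45%, 1 − 0.44 = 56%, 1 − 0.37 = 63% at zero.
- Conditioned on having at least one of the three, assuming independence: P(any) = 1 − 0.45 × 0.56 × 0.63 = 0.841. The shares become 0.55/0.841 = 65%, 0.44/0.841 = 52% and 0.37/0.841 = 44%, so 35%, 48% and 56% are at zero.

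The working range is therefore 35-63%.

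**3. Closed-form check.** Further assumptions: a 0-10 scale; symptomatic women with mean 6, SD 2.5 and pre-post correlation 0.5; other women at zero throughout; an effect of 0.75 × 2.5 = 1.875 points in symptomatic women only. Let p be the share with the symptom. The mean difference is 1.875p.
- Final values: symptomatic means are 6 (control) and 4.125 (treated), so the average variance is 6.25p + p(1−p)(36 + 17.02)/2. For p = 0.55 this is 3.44 + 6.56 = 10.00, giving d = 1.031/3.162 = 0.326. Power is 24%, 18% and 15% for p = 0.55, 0.44 and 0.37.
- Change: the variance of change in symptomatic women is 2(1 − 0.5) × 6.25 = 6.25, so the average variance is 6.25p + p(1−p) × 3.516/2. For p = 0.55 this is 3.44 + 0.44 = 3.87, giving d = 1.031/1.968 = 0.524. Power is 51%, 42% and 36%.

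**4. Simulation under the same assumptions** (30 per group, scores limited to 0-10, 35-63% at zero). A repeat run agreed to within about 3 percentage points.

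| Analysis | 0.75 SD effect | 1.0 SD effect |
|---|---|---|
| Final values (t-test or Mann-Whitney) | 8-30% | 9-50% |
| t-test on change | 36-61% | 56-83% |
| Baseline-adjusted | 42-71% | 67-92% |

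When every woman has the symptom, the baseline-adjusted analysis at 0.75 SD gives 90%.

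**5. Sensitivity, half of women at zero.** Effects of 0.75 / 1.00 / 1.25 SD:

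| Analysis | Mean 6, SD 2 | Mean 4, SD 2.5 |
|---|---|---|
| t-test, final values | 16 / 24 / 37% | 27 / 46 / 65% |
| Mann-Whitney, final values | 12 / 15 / 20% | 16 / 29 / 43% |
| t-test, change | 49 / 69 / 83% | 45 / 64 / 78% |
| Baseline-adjusted | 56 / 80 / 94% | 57 / 81 / 94% |

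With only 25% at zero (mean 6, SD 2) and a 1.0 SD effect, the t-test on change gives 89% and the adjusted analysis 95%, while both final-value tests give 55%.

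**6. Which route the plan favours.** A scale with a large cluster of zeros is likely to fail Shapiro-Wilk, and the plan then moves to Mann-Whitney. On final values that is the weakest row above. Mann-Whitney on change was not calculated.

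**The case against.** The strongest reply is that the protocol never says all women are compared on every scale. The analysis set for each scale, and the choice between final value and change, may stand in an analysis plan that is not shown. That is fair, and silence on those details is not the point. What the protocol does fix is an entry rule open to any one symptom and separate scales for each symptom. A later plan cannot reliably recover which symptom bothered each woman most before treatment. Restricting a scale to women with the symptom does not restore power either: with half affected, about 15 per group remain, and a t-test on final values has 50-52% power at 0.75 SD.

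Several stronger conclusions are tempting but not supported.
- A reader might infer that about half of the women will score zero on any given scale. The frequencies come from other populations and cover three symptoms. Entrants are selected for symptoms and may have several, and having no complaint in a survey is not the same as a VAS of exactly zero.
- A reader might infer almost no power. That fits only final-value analyses at the smaller effects. With half at zero, power runs from about 12% to 94% across analyses and planned effects.
- A reader might infer that every scale will miss a real benefit. On the change-score powers above, and assuming independence, the three costed scales all miss with probability 0.49 × 0.58 × 0.64 = 18%. Correlation between scales would raise this, but it does not make it the expected result.
- A reader might infer that the question on GSM is left unanswered. The Vaginal Health Index and the sexual function index also address it, and the VAS is not named primary.
- A reader might infer that the dyspareunia scale has no valid second reading in many women, from the background figure "72% of women having intercourse only once a month". That figure describes another population and adds to more than 100% with the weekly figure beside it (72% + 34% = 106%). No VAS recall period is stated.

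**Conclusion.** The concern holds in a limited form. Because entry needs only one GSM symptom, possibly a urinary one, women without a given symptom dilute its VAS comparison. The per-symptom comparisons may then have well under 80% power at the smallest effect the plan considers. Under the assumptions in steps 2 to 4 of the working, every analysis falls short at 0.75 SD. At 1.0 SD final values still fall short, while change and adjusted analyses range from short to adequate. At 1.25 SD with half at zero, the adjusted analysis shows no shortfall. The symptom shares, VAS means and SDs, the correlation of 0.5 and the fixed zeros are all assumptions; the protocol supplies none of them for its own cohort. The point is worth acting on because the remedy is cheap and must be in place before randomisation. It does not show that the trial as a whole is underpowered.

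**What to change.** Before randomisation, ask each woman which of the VAS-rated symptoms bothers her most, and record it. Make the VAS of that symptom the single symptom comparison, analysed by ANCOVA on the baseline score. Women with no VAS-rated symptom do not contribute to it; the protocol should say so. Report the individual scales as secondary or descriptive, baseline-adjusted, in women whose baseline score is above zero.

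The 90% power for the adjusted analysis assumes that all 30 women per group nominate a symptom and respond equally. There is some room: with correlation 0.5 the adjusted effect is 0.75/√(1 − 0.25) = 0.866, and 80% power needs about 2 × (1.96 + 0.84)²/0.75 = 21 women per group by the normal formula. Extra variability from mixing symptoms would raise that number.

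Cost: one baseline question and a few sentences of analysis wording. The pooled outcome mixes symptoms, so claims about a single symptom become descriptive, and women with urinary symptoms only are left to the urinary outcomes.

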#### Vulvar temperature

The vulvar temperature measured in degrees Celsius, will be evaluated at the same eight points that were irradiated in the vulvar region using a digital infrared thermometer, allowing for non-contact measurements. The average of the eight readings will be calculated before and after each of the four consecutive weekly sessions of diode laser treatment.

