**Method:**

In this randomized, double-blind, placebo-controlled study protocol, women over 50 years of age who are in the postmenopausal period (amenorrhea for at least 12 months, with no pathology involved) with one or more symptoms of GSM will be randomly divided into two groups. The treatment group (n = 30) will receive four consecutive applications, weekly, using DMC laser diode (λ = 808 nm), 4J per point, 100mW of power, 1,016W/cm^2^, 8 sites in the vulvar region, The Placebo Group (n = 30) will be handled as treated, but with the laser turned off. The quality of life will be assessed using female sexual functioning index (FSFI-6), urinary incontinence questionnaire (ICIQ-SF), Quality of life will be analyzed using the female sexual functioning index (FSFI-6). The intensity of menopausal symptoms will be evaluated using a visual analogue scale (VAS), the vulvo vaginal atrophy will be measured by the Vaginal Health Index (VHI). Also, the vaginal temperature will be measured using a thermal camera, the pressure of the pelvic floor force (vaginal dynamometer) and a 1-hour Pad Test will be performed to quantify the urinary loss. With this procedure, we intend to obtain an overall better life quality and diminished symptoms in women with GSM. All assessments will be performed prior to the first irradiation and after the last one.

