## Study limitations

The main limitation of this study is the short evaluation period of 90 days, which may be insufficient to determine the long-term efficacy and durability of photobiomodulation therapy for treating GSM symptoms. Additionally, the reliance on self-reported data could potentially introduce bias due to subjective interpretations and reporting inaccuracies by participants.

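### The Abstract and the Methods conflict on the site, device and schedule of the temperature outcome, and the value to be compared between arms is not fixed

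*Protocol article*

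**What the plan says.** The two descriptions of temperature are both current text, and neither is marked as replaced.

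- **Abstract, Method.** It states that "the vaginal temperature will be measured using a thermal camera". On timing, for every measure: "All assessments will be performed prior to the first irradiation and after the last one".
- **Methods, Outcomes, Vulvar temperature.** Temperature "will be evaluated at the same eight points that were irradiated in the vulvar region using a digital infrared thermometer". On timing: "The average of the eight readings will be calculated before and after each of the four consecutive weekly sessions of diode laser treatment".
- **Methods, Statistical analysis.** Arms are compared with Student's t-test or the Wilcoxon-Mann-Whitney test, two-sided at 0.05. No temperature value or change score is named.
- **Photobiomodulation protocol and Table 1.** Each of the eight points receives 4 J (100 mW for 40 s), 32 J per session. In the sham arm the laser stays off.
- **Study limitations.** "The main limitation of this study is the short evaluation period of 90 days".

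The name of the sexual-function instrument also differs. The Abstract writes FSFI-6, while Methods, Questionnaires has: "The Female Sexual Function Index (FSFI) is a tool used to evaluate female sexual response across six domains".

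**The concern.** One outcome is defined in two ways that cannot both be followed. Someone collecting the data would not know where to measure, with what, or how often. Someone reading the results could not tell whether the reported temperature contrast was the one planned.

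The schedule matters most for the analysis. The Methods produce eight session means per woman, while the only stated tests take one value per woman. Several quite different questions could be answered with those means: drift across weeks, change over the whole course, or the response within a session.

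The after-session means raise a further difficulty of interpretation. They are read at the spots where the device has delivered energy in one arm and none in the other. An arm difference in those readings could reflect a short-lived local effect of the device, a lasting change in the tissue, or both, and the reading alone cannot separate them.

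**Working it through.** **1. The two descriptions side by side**

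| Feature | Abstract | Methods, Vulvar temperature |
|---|---|---|
| Site | vaginal | vulvar, the eight irradiated points |
| Device | thermal camera | non-contact infrared thermometer |
| Occasions | 2 | 4 sessions × 2 = 8 |
| Summary | not stated | mean of eight readings |

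The first three rows conflict. Condensing a protocol into an article explains omissions, but not two different positive statements.

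**2. What the Methods schedule yields.** Write B1 to B4 for the means before sessions 1 to 4, and A1 to A4 for the means after them. That is 8 means per woman, each from 8 readings, so 8 × 8 = 64 readings. One mean (B1) precedes all treatment. Four (A1 to A4) follow a session.

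**3. Candidate values for a two-group test.** Each of these is one number per woman, so each fits the stated tests:

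- A4 alone, the last reading
- A4 − B1, the only change available under the Abstract's schedule
- B4 − B1, change across weeks from pre-session readings
- As − Bs for a session s, the within-session change

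They are linked by A4 − B1 = (B4 − B1) + (A4 − B4). The Abstract's first-to-last change is thus the between-session change over three sessions plus the within-session change at session 4. Where the arms differ in the second term, the total does not show how much of the difference would outlast the visit.

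**4. Energy at the measured points.** Table 1 reproduces: 0.1 W × 40 s = 4 J per point, and 8 × 4 J = 32 J per session. In the sham arm it is 0 J. The after-session readings sit on these same points. The documents give no interval between the end of irradiation and the reading, and no expected temperature rise, so the size of any local effect cannot be computed.

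**5. Sessions completed at each candidate endpoint.** B4 reflects 4 − 1 = 3 completed sessions. A4 reflects all four, but at an unstated interval after the fourth. Neither is a reading after the full course that is clearly separate from an acute effect.

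**6. The 90-day period.** With weekly sessions, the fourth falls (4 − 1) × 7 = 21 days after the first. Neither temperature schedule contains a reading near 90 days, so this is a third time frame to reconcile.

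**7. Sample size.** With a standardised effect of 0.75, n = 2 × (1.960 + 0.842)² / 0.75² = 27.9, so 28 per group. The t-test version gives 28.9, so 29. Power with 30 per group is 0.828 (normal) or 0.815 (t-test), in line with the stated value above 0.80. Nothing in this calculation refers to temperature, so it does not change.

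**The case against.** The Methods are the operative text and are specific. The Abstract is a one-line summary, and the article uses vaginal loosely elsewhere: the irradiation text speaks of the vaginal region where Table 1 says vulvar. The site conflict may therefore be one of wording. This has some force for site, but it does not explain two different devices or 2 against 8 occasions.

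The choice of analysed time point is commonly left to an analysis plan, which is not shown, and a t-test on one change score per woman is compatible with the stated analysis. Taken alone, the missing choice would not be a finding. It matters here because the two schedules disagree on which readings will exist, so the document does not settle what any such choice would be made from.

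The article offers vasodilation as a mechanism of the treatment, so a before-to-after skin reading may be an intended measure of acute response. That is fair, and it is a reason to report that change under its own name.

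Some stronger readings are tempting but are not supported:

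- **Heating explains any temperature result.** No interval and no size of warming are given. The documents support only that after-session readings may mix the two effects.
- **The false-positive rate is inflated by testing each session mean.** No such set of tests is planned, and the mean before session 1 cannot be a test of treatment. No figure should be attached.
- **Data will be collected with two devices.** Nothing plans this; the two sections simply name different ones.
- **Two sexual-function instruments are in use.** FSFI-6 and an FSFI with six domains may be one instrument loosely named.

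**Conclusion.** The contradiction is certain. For one outcome, the Abstract and the Methods disagree on site, on device and on schedule (2 against 8 occasions), and an unseen analysis plan would not remove a conflict inside this article. It follows that the value entering the two-group test cannot be identified from the text. That after-session readings may combine an acute local effect with lasting change follows from the design, because they are taken at points irradiated in one arm only; how large that effect is cannot be said.

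The reach is limited. Temperature is not named as primary, and the sample size stays at 60. The FSFI label is a minor matter of wording. The correction should be made because it costs little, and without it the temperature result can be read in several ways.

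**What to change.** 1. Make the Abstract and the Methods state the same site, the same device and the same schedule for temperature, and explain how the 90-day evaluation period relates to it. If readings have already been taken, state what was actually used.
2. Name one temperature contrast for the comparison between arms. Replace the unadjusted two-group test for this outcome with a comparison adjusted for the pre-irradiation mean at session 1, for example a linear model with arm and that baseline.
3. Report within-session change (before to after) separately as an acute response, not as the treatment-effect contrast, and state the interval between the end of irradiation and the reading.
4. If the pre-irradiation reading at session 4 is chosen as the endpoint, state that it reflects only three completed sessions.
5. Use one FSFI name in both places.

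**Cost.** This is wording only if the Methods schedule is kept, since all the readings named here are already planned under it. The price is that after-session readings no longer serve as the main evidence on temperature. An endpoint before session 4 leaves the last application unassessed, while a separate reading after the full course would add a visit. If the Abstract's two-occasion schedule is kept, no pre-session reading after baseline exists, so the interval after the last irradiation must be fixed and the mixing of acute and lasting change acknowledged.
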